### Outcomes

Primary outcomes: to evaluate the antivenom safety profile through laboratory and clinical adverse events; to verify the proportion of individuals with improvement in the initial clinical picture by monitoring signs, symptoms and laboratory exams.Secondary outcomes: to evaluate the degree de correlation between the number of stings and the severity of the initial clinical picture (APACHE II).Exploratory outcomes: to evaluate the pharmacokinetic and immunogenic profile of antivenom/venom at doses established by an analysis of the blood samples collected at different moments (before and at 2, 6, 12 and 24 h after heterologous serum therapy); to evaluate the proteomic profile of the antivenom as determined by the differential expression of the proteins albumin, C-reactive protein (CRP) and fibrinogen, by the presence of the components melittin and phospholipase A_2_, and by the heterologous serum protein profile of the degradome and peptide/protein biomarkers.

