### Objectives

Primary objectives: to evaluate the safety of the antivenom including number and severity of acute adverse events, as well as deaths suspected to be related to the intervention; and to confirm the lowest effective dose when faced with different quantities of venom inoculated in patients exposed to multiple stings from Africanized honeybees.Secondary objectives: to correlate the severity of the initial clinical condition with number of stings.Explanatory objectives: to evaluate the antivenom neutralizing power by pharmacokinetic and proteomic studies; and to evaluate the antivenom pharmacokinetics and immunogenicity.

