#### Risks and benefits

Risks:Acute hypersensitivity to heterologous serum.Adverse events intrinsic to heterologous serum.Delayed hypersensitivity to heterologous serum.
Benefits:Neutralization of inoculated venom, with interruption of its toxicity.Support to anaphylactic reactions related to envenomation.

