### Subsidiary laboratory tests

To evaluate the safety parameters, tests will be required on hospitalization days one, two, five and ten, and at follow up (10, 20 and 30 days after hospital discharge) (Table 1).

**Table 1 Tab1:** Laboratory tests requested during hospitalization and follow-up

Procedures	HOSPITALIZATION			FOLLOW-UP		
	Day 1	Day 2	Hospital discharge	Return 1 (R1) (10 days after discharge)	Return 2 (R2) (20 days after discharge)	Return 3 (R3) (30 days after discharge)
Application of FICT	X					
Demographic data	X					
Clinical history	X					
Clinical exam	X	X	X	X	X	X
Concomitant medications	X	X	X	X	X	X
Adverse events	X	X	X	X	X	X
Vital signs	X^a^	X	X	X	X	X
Hemogram	X	X	X	X	X	X
Urine type I	X^b^	X	X	X	X	X
Urea	X	X	X	X	X	X
Creatinine	X	X	X	X	X	X
AST	X	X	X	X	X	X
ALT	X	X	X	X	X	X
Alkaline phosphatase	X	X	X	X	X	X
Gama GT	X	X	X	X	X	X
Bilirubin (direct)	X	X	X	X	X	X
Bilirubin (indirect)	X	X	X	X	X	X
Fasting blood sugar	X	X	X	X	X	X
Cholesterol (total and fractions)	X	X	X	X	X	X
Fibrinogen	X^b^	X	X	X	X	X
C-reactive protein	X^b^	X	X	X	X	X
ESR	X^b^	X	X	X	X	X
PT	X^b^	X	X	X	X	X
APTT	X^b^	X	X	X	X	X
CPK	X^b^	X	X	X	X	X
Albumin	X	X	X	X	X	X
Globulin	X	X	X	X	X	X
Pharmacokinetic profile	X^c^	X	X	X	X	X
Proteomic profile	X^d^	X	X	X	X	X
Pregnancy test	X^e^					

*FICT* free and informed consent term, *AST* aspartate aminotransferase, *ALT* alanine amino transferase, *gama GT*: gamma glutamyl transferase, *CRP* C-reactive protein, *ESR* erythrocyte sedimentation rate, *PT* prothrombin time, *APTT* activated partial thromboplastin time, *CPK* creatine phosphokinase

^a^The vital signs should be taken every 30 min during the infusion and every hour through the first 12 h after the infusion

^b^Collect before and 12 h after termination of the infusion

^c^Evaluate the profile and level of the antibodies IgG and IgM against the antivenom infusion (before and at 2, 6, 12 and 24 h after infusion)

^d^Evaluate the profile of the different heterologous serum proteins in the antivenom (before and at 2, 6, 12 and 24 h after infusion)

^e^In special cases and at the investigator’s discretion this test could be repeated

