Complementing the results of the laboratory exams, a proteomic evaluation will also be performed by degradome analysis, seeking to evidence eventual biomarkers responsible for physiological and clinical alterations [16, 17]. Furthermore, a pharmacokinetic profile of venom and of a new antivenom will be performed utilizing immunoenzymatic methods (ELISA) due to their sensitivity, reproducibility, ease of execution and low cost. Thus, the trial denominated “venenomia” will have the objective of determining the kinetics of circulating toxins and antivenom, aiding in the diagnosis, in the determination of accident severity and in the evaluation of heterologous serum therapy efficacy [18–20].

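### The exploratory immunogenicity outcome stops at 24 h, out of step with Table 1, and the article gives two different analytes for the pharmacokinetic profile

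*Protocol article*

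**What the plan says.** The Objectives section names two separate aims in its third tier: "to evaluate the antivenom pharmacokinetics and immunogenicity". The Outcomes section merges them into one exploratory outcome on antivenom and venom, taken from blood samples "collected at different moments (before and at 2, 6, 12 and 24 h after heterologous serum therapy". No later time is named for either component.

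Table 1, under Subsidiary laboratory tests, has no row for immunogenicity. Its pharmacokinetic row is marked in all six columns: Day 1, Day 2, discharge, and Returns 1, 2 and 3 (10, 20 and 30 days after discharge). The Day 1 mark carries footnote c: "Evaluate the profile and level of the antibodies IgG and IgM against the antivenom infusion", again before and at 2, 6, 12 and 24 h.

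The text after Table 1 describes the pharmacokinetic profile differently. It is an ELISA of venom and of the antivenom, meant to determine "the kinetics of circulating toxins and antivenom".

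Among the risks, the article lists "Delayed hypersensitivity to heterologous serum", and its Conclusions class heterologous serum disease as a late reaction.

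**The concern.** There are two separate faults.

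**Timing.** One schedule serves two quantities that change on different time scales. Venom and antivenom concentrations move over hours, so sampling to 24 h is reasonable for them. A treatment-induced antibody response to horse protein develops over days. An immunogenicity result computed strictly from the stated outcome would describe the antibody that patients brought with them. It could then be reported as little or no immunogenicity when the response had simply not been observed yet.

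**Analyte.** Anti-antivenom IgG/IgM and circulating venom or antivenom are different measurements, and the article puts both under the same pharmacokinetic label. Centres working from Table 1 and centres working from the text would have different ideas of what the early samples are for. With 20 participants, there is little room to lose samples to a misunderstanding.

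**Working it through.** No sample size, power or error rate bears on this point, so the check compares sampling times and assay definitions.

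**Inputs**

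- Outcome window: pre-infusion, 2, 6, 12 and 24 h (Outcomes).
- Scheduled samples: Day 1, Day 2, discharge, and discharge + 10, + 20 and + 30 days (Table 1).
- Infusion time: within two hours (Specific treatment).
- Onset of a new anti-antivenom antibody response: not given. Assumed about 5 to 14 days in a person not previously exposed and about 3 to 7 days after earlier exposure to horse protein, so 3 to 14 days overall.
- Day of discharge: not given. Assumed day 2 to day 10, the span from the second to the last in-hospital test day named in the text above Table 1.

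**Step 1. Outcome window against onset.** The last outcome sample is at 24 h, or 1 day. The earliest assumed onset is 3 days = 72 h, and 72 / 24 = 3. The latest is 14 days = 336 h, and 336 / 24 = 14. The last sample would come too early by a factor of 3 to 14, so the conclusion does not depend on where in the range the true onset lies.

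**Step 2. Scheduled late samples against onset.** Visit day = discharge day + 10, 20 or 30.

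| Sample | Discharge on day 2 | Discharge on day 10 |
|---|---|---|
| Discharge | 2 | 10 |
| Return 1 | 12 | 20 |
| Return 2 | 22 | 30 |
| Return 3 | 32 | 40 |

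Returns 2 and 3 fall after the whole assumed range. Return 1 falls on day 14 or later once discharge is on day 4 or later, and only slightly short of day 14 otherwise. The discharge sample may fall before or within the range, depending on length of stay. Visits are anchored to discharge, so the same visit label can differ by 8 days between patients (10 − 2). Late samples therefore need to be analysed by days since infusion.

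**Step 3. What footnote c covers.** The superscript sits on the Day 1 cell only, which leaves two readings.

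- *It defines the whole row.* Antibodies are then scheduled through Return 3, but the outcome still stops at 24 h, and no row of Table 1 names the venom and antivenom concentrations that the text promises.
- *It defines Day 1 only.* The 2 to 24 h samples, where concentration curves are needed, are then assigned to antibodies, and the marks from Day 2 on have no stated analyte.

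Each reading leaves Table 1 inconsistent with the text.

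**Step 4. Time zero.** Footnote b counts from the end of the infusion. The outcome and footnotes c and d say only that samples follow the therapy or infusion. With a full two-hour infusion, the 2 h sample is at the end of infusion if time runs from the start, or 4 h after the start (2 + 2) if it runs from the end. For a concentration curve these are different points.

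**The case against.** The strongest reply is that the plan as a whole is sounder than its outcome sentence, and that a journal article condenses a full protocol in which assay procedures would normally sit. Much of this stands, and it rules out several stronger conclusions that a reader might draw.

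- *That the trial cannot observe immunogenicity at all.* Table 1 marks the row through Return 3, and if footnote c covers the row, late antibody samples are planned. The limit applies to the outcome definition.
- *That the concentration curves may never be produced.* The text after Table 1 commits to an ELISA of venom and antivenom, and the outcome mentions both.
- *That these curves are the only direct evidence on neutralising power.* The Objectives assign neutralising power to pharmacokinetic and proteomic studies together, and the proteomic outcome looks for melittin and phospholipase A2.
- *That all five samples are uninformative.* The pre-infusion sample is the baseline that any change needs. Pre-existing antibody is also of interest, because the exclusion criteria bar a previous reaction to horse serum but not all previous exposure.
- *That delayed hypersensitivity could not be related to antibody levels.* Table 1 schedules both samples and adverse-event recording at Returns 1 to 3, and no objective requires that link.

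The reply does not remove the two faults. The outcome names its sampling times explicitly, and they end at 24 h. Footnote c and the text after Table 1 name different analytes under one label. Both are statements within the article and not details left to another document.

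**Conclusion.** The point holds in a limited form. The immunogenicity part of the exploratory outcome is tied to a window that ends at 24 h, and its four post-infusion samples can show only pre-existing antibody. This rests on an assumed onset of about 3 to 14 days, which the documents do not give, and it would fail only if induced antibody appeared within one day. The article's own description of serum disease as a late reaction points the same way. The outcome definition and Table 1 disagree on how long sampling lasts, and Table 1 and the text disagree on what the pharmacokinetic profile measures, whichever way footnote c is read.

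Severity is low. The outcome is exploratory, and no primary or secondary outcome depends on it.

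**What to change.** 1. In Outcomes, split the exploratory outcome in two.
   - Pharmacokinetics: venom and antivenom concentrations before and at 2, 6, 12 and 24 h, stating whether time runs from the start or the end of the infusion.
   - Immunogenicity: change in anti-antivenom IgM and IgG from the pre-infusion sample to discharge and Returns 1 to 3, analysed by days since infusion because the visits are anchored to discharge.
2. In Table 1, reconcile footnote c with the ELISA description, so that the pharmacokinetic row names venom and antivenom. Give immunogenicity its own row at baseline, discharge and Returns 1 to 3.

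The cost is wording in one outcome and one table, plus a few antibody assays on late samples already scheduled. No new visit is needed, and treatment is not affected.

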### Study participation agreement

Prior to the performance of any procedure related to the study, the participants in the research and/or their family members must be informed about its objectives, risks and procedures. Those who consented to participate must sign, date and initial the terms of free and informed consent (TFIC). The process of obtaining the TFIC must be documented on the patient’s chart. If the consent and signature of the patient are impossible to obtain, by virtue of his or her clinical condition, it is essential to locate a family member or other responsible party to provide them.

### Approval from regulatory agencies

#### Approval from the Research Ethics Committee (CEP)

The National Commission for Ethics on Research (CONEP) approved the clinical research protocol and the terms of free and informed consent (TFIC). The investigators of the other centers must send to the coordinating center a copy of the approval by the local research ethics committee (CEP) of the current version of the clinical study protocol, the TFIC and its necessary revisions. The coordinating CEP-CONEP system will oversee the conduct of the study.

#### Approval from the management of ANVISA Clinical Research

The National Health Surveillance Agency (ANVISA), through intermediation of the General Management of Drugs department, received all documentation of the product, including the clinical research protocol, the guide for researchers (a complete history of the development of the product) and the other documents necessary for analysis and approval. This is the first time that an antivenom against bee stings is evaluated in human’s clinical trial.

#### Registration in the ReBec

The Brazilian Clinical Trials Registry (ReBec) is a virtual platform of free access to a registry of experimental and non-experimental studies performed on humans and conducted on Brazilian territory, by Brazilian and foreign researchers. ReBec is a joint project of the Ministry of Health (DECIT/MS), the Pan American Health Organization (PAHO) and Oswaldo Cruz Foundation (FIOCRUZ). The executive committee of ReBec is composed of the abovementioned institutions and ANVISA. The *Apis* study was registered in ReBec http://www.ensaiosclinicos.gov.br/.

### Centers participating in the study

All the Brazilian research centers registered in the National Clinical Research Network (RNPC) will be invited to participate.

### Statistical analysis

The statistical analysis, as well as the choice of tests for comparison among the research participants, will be executed with respect to the presuppositions determined by the results, characteristics and behavior of the variables in the study. The binomial variables will be compared by chi-square and Fisher’s exact test. The numerical variables will be compared by the Student’s *t* test or *U* test of Mann–Whitney [13, 14].

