### Design of the *Apis* study

This is a multicenter, non-randomized and open phase I/II clinical trial study to evaluate the safety, determine the pharmacokinetic and proteomic profile, and confirm the lowest antivenom dose, according to the severity of each case. It will include 20 adult individuals, of both sexes, afflicted with multiple stings from Africanized *Apis mellifera* honeybees. The study population will be of the type non-probabilistic by convenience (or accidental) sample, given the low demographic density of the studied phenomenon and the extreme geographic decentralization of this event. The sample size was estimated by considering examples of phase I/II clinical studies proposing to study the safety and neutralizing power and to confirm the minimum required dose of antivenom [12]. Not performing the sample calculation is justified by the fact that the efficacy outcome is not the target at this moment given that there are no data on safety and adequate dose. The study will last 36 months, with 24 months for recruitment.

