### Plan of treatment (specific, adjuvant, symptomatic and complementary)

#### Specific treatment

The *WHO Guideline for the production control and regulation of snake antivenom immunoglobulins* [12] suggests that the protocol prepared for the specific treatment be based on the estimated quantity of venom inoculated by the bee and on the neutralizing capacity of the antivenin. Thus, the authors suggested:Up to 5 stings: specific treatment is not indicated, except for a medical criterion.Between 5 and 200 stings: two vials of apilic antivenom.Between 201 and 600 stings: six vials of apilic antivenom.Above 600 stings: ten vials of apilic antivenom.

After the dose is determined by the attending medical team, the vials must be opened and their content aspirated by means of a syringe. Next, insert all the content into a flask containing 250 mL of normal 0.9% saline solution, previously emptied. This flask containing the antivenom must be connected into a Y formation with another flask containing 250 mL of 0.9% saline. One large-caliber vein of the forearm must be catheterized and these two contents need to be infused in the Y within two hours. All patients must be hospitalized and monitored throughout the infusion by the continuous presence of the hospital staff at the patient’s bedside. The team must also have at their disposal the drugs and equipment necessary for the treatment of mild or severe adverse reactions. Any adverse events and signs and symptoms of possible toxicity must be noted on the patient’s chart.

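### The statistical section names tests that compare participants with one another, but the stated outcomes are one-sample proportions, within-patient changes and a correlation

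*Protocol article*

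**What the plan says.** **Design.** Under Design of the *Apis* study, the trial is a "multicenter, non-randomized and open phase I/II clinical trial". On size, "It will include 20 adult individuals, of both sexes". No control or comparator group is described. No sample size was calculated: "Not performing the sample calculation is justified by the fact that the efficacy outcome is not the target at this moment".

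**Dose.** Under Specific treatment, the number of vials follows the sting count. The lowest treated band reads "Between 5 and 200 stings: two vials of apilic antivenom"; the two higher bands receive six and ten vials.

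**Outcomes.** The Outcomes section lists:
- primary: a safety profile from clinical and laboratory adverse events, and the proportion of individuals whose initial clinical picture improves;
- secondary: the "correlation between the number of stings and the severity of the initial clinical picture", measured by APACHE II;
- exploratory: pharmacokinetic, immunogenic and proteomic profiles from blood taken before and at 2, 6, 12 and 24 h after treatment.

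Table 1 (Subsidiary laboratory tests) adds a before and 12 h-after pair for urine, fibrinogen, CRP, ESR, PT, APTT and CPK, with further values up to 30 days after discharge.

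**Analysis.** "The binomial variables will be compared by chi-square" and Fisher's exact test, and numerical variables by Student's t or Mann-Whitney U. The purpose is given as comparison among participants ("the choice of tests for comparison among the research participants, will be executed with respect to the presuppositions determined by the results"). No groups are named.

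**The concern.** The section makes a positive statement about tests, and that statement does not fit the outcomes listed a few paragraphs earlier. A proportion in one treated group calls for an estimate with an interval. Values before and after infusion in the same patient call for a method that uses the pairing. A correlation calls for a correlation coefficient.

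An analyst who follows the section literally has two routes, and both are poor:
- Treat the before and after values as two independent samples. This discards the pairing, and with 20 patients a real laboratory change is more easily missed.
- Compare sting bands. Dose rises with sting count by design, so any difference between bands mixes dose with the amount of venom. One primary objective is to confirm the lowest effective dose, so such p-values could easily be taken as evidence about dose.

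**Working it through.** **1. Stated outcomes against named tests**

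| Outcome | What it requires | Named in the section |
|---|---|---|
| Adverse-event profile | One-sample rates with intervals | Chi-square, Fisher |
| Proportion improved | One-sample proportion with interval | Chi-square, Fisher |
| Stings versus APACHE II | Correlation with interval | None |
| Before/after and serial values | Paired or repeated-measures method | Student's t or Mann-Whitney U |

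Mann-Whitney U and Fisher's test cannot use pairing. Student's t can in its paired form, but the section does not say so, and its stated purpose and the alternative offered (U) point to the two-sample form.

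**2. Cost of ignoring the pairing**

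There is no figure in the plan to reproduce. From the documents: n = 20. Assumed: two-sided 5% level, equal variances, normal values, within-patient correlation r, mean change 0.5 SD.

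- The true variance of the mean change is 2(1 − r)SD²/n; the two-sample test uses 2·SD²/n. Its standard error is too large by 1/√(1 − r): 1/√0.5 = 1.41 at r = 0.5 and 1/√0.3 = 1.83 at r = 0.7.
- Paired test: noncentrality = √20 × 0.5/√(2(1 − r)), with 19 degrees of freedom. At r = 0.5 this is 4.472 × 0.500 = 2.24; at r = 0.7 it is 4.472 × 0.645 = 2.89.
- Size and power of the two-sample test come from simulation (200,000 runs per setting).

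| Assumed r | True size, unpaired | Power, unpaired | Power, paired |
|---|---|---|---|
| 0.3 | 2.1% | 31% | 43% |
| 0.5 | 0.8% | 28% | 56% |
| 0.7 | 0.1% | 25% | 78% |

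The error is conservative: too few false positives, at the price of lost power.

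**3. What matching methods would give with 20 patients**

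- Exact (Clopper-Pearson) upper 95% limit for 0/20 events: 1 − 0.025^(1/20) = 16.8%.
- Exact 95% interval for an illustrative 16/20 improved: 56.3% to 94.3%.
- Interval for an illustrative correlation of 0.5, by Fisher's z: tanh(0.549 ± 1.96/√17) = 0.07 to 0.77. This is approximate for a rank correlation.

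**4. Sting bands as groups**

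There are three bands. Student's t and U compare two groups at a time, while chi-square can handle three. Whichever test is used, the dose in each band is set by the sting count, so dose and venom load cannot be separated.

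**The case against.** Several counter-arguments carry weight.

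- **A reader might infer that tests will be picked after seeing which gives the better answer.** The text does not support that. The full sentence goes on to the characteristics and behavior of the variables, and t or U follows as a pair of alternatives. The natural meaning is a choice by distribution. What remains is that no rule for that choice is stated.
- **A reader might infer that every named test is for independent groups.** That is too strong. Student's t has one-sample and paired forms, and chi-square has a one-sample form. The section never says unpaired, and never says that before/after data will go through these tests.
- **Missing interval and correlation methods are partly analysis-plan detail.** This is a condensed article, and the full protocol and analysis plan are not shown. Their absence alone is no fault. The point rests on the tests that are named and the purpose given for them.
- **Some groups do exist.** The treatment sections split patients by sting band and by presence of anaphylactic shock, and the latter is a two-group split that these tests would fit. Neither split is designated as a comparison, and neither corresponds to a stated outcome.
- **Small cells are covered**, since Fisher's test is named.
- **The size of the loss depends on assumed inputs**, efficacy is said not to be the target, and the 16.8% limit follows from n = 20 whichever test is used. All true. Safety is a target, however, and laboratory change is part of it.

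**Conclusion.** The mismatch between the named tests and the stated outcomes holds. It touches both primary outcomes, the only secondary outcome and the serial measurements. It is a moderate fault of wording: no stated number is wrong, and no data would be lost.

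The size applies only if the t test is used in its two-sample form on paired values. Over an assumed correlation of 0.5 to 0.7 and a 0.5 SD change, power then falls from 56%–78% to about 28%–25%. At a correlation of 0.3 the loss is smaller, from 43% to 31%.

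Two readings rest on inference. That there is a single treated group follows from the absence of any described comparator; the article does not use the term. That within-patient change matters follows from the improvement outcome and the before/after sampling; paired change is not named as an endpoint. The documents do not show that between-band p-values are planned, only that the section as worded allows them and gives no caution.

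**What to change.** Rewrite the Statistical analysis section so that each outcome has a matching method:

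- **Adverse-event and improvement proportions:** exact 95% intervals, with a note that 0/20 events is still compatible with a true rate up to 16.8%.
- **Before/after and serial values:** paired t or Wilcoxon signed-rank, McNemar for binary changes, or a mixed model for repeated laboratory, venom and antivenom values.
- **Sting number versus APACHE II:** Spearman correlation with a 95% interval.
- **Sting bands:** descriptive results; label any between-band comparison as confounded by severity and venom load.
- **Parametric or non-parametric:** state the rule and fix it before the data are seen.

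If a full analysis plan already does this, bring the published section into line with it. The cost is wording only. Sample size, visits, sampling and treatment stay as they are.
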